## Abstract

**Background:**

Transcutaneous tibial nerve stimulation (TTNS) and percutaneous tibial nerve stimulation (PTNS) are effective and safe therapies for overactive bladder (OAB) syndrome in adults. However, few randomized sham-controlled trials have been conducted in a pediatric population. To our knowledge, both therapies never have been compared in children.

**Aim:**

The aim of the complete study is twofold: (1) to assess the efficacy of TTNS therapy on bladder symptoms after 12 weeks of treatment in a pediatric population with idiopathic overactive bladder syndrome (iOAB) and/or nocturnal enuresis (part I) and (2) to assess the effect of TTNS compared to PTNS (part II). In this article, we aim to present the protocol of the first part of the TaPaS trial (TTNS, PTNS, sham therapy).

**Methods:**

Part I of the TaPaS trial is set up as a single-center randomized-controlled trial. Children, aged from 5 to 12 years with iOAB and/or nocturnal enuresis, are assigned to two groups by computer-generated randomization: TTNS therapy (intervention) and sham therapy (control). The primary outcome is the percentage difference in average voided volume (AVV) between baseline and after 12 weeks of treatment. Secondary endpoints are the percentage difference in supervoid volumes, number of urinary incontinence episodes/24 h and in voiding frequency, the difference in parent reported outcomes between baseline and after 12 weeks of treatment, and the duration of clinical response.

**Discussion:**

We hypothesize that TTNS is a non-inferior treatment for iOAB in children compared to PTNS therapy. Since literature is inconclusive about the efficacy of TTNS in a pediatric population, a sham-controlled RCT on TTNS will be conducted (part I). A protocol for a prospective randomized sham-controlled trial has been developed. Enrolment has started in November 2018. Study completion of part I is expected by August 2021.

**Trial registration:**

ClinicalTrials.gov NCT 04256876. Retrospectively registered on February 5, 2020.

**Supplementary Information:**

The online version contains supplementary material available at 10.1186/s13063-021-05117-8.

## Administrative information

The order of the items has been modified to group similar items (see http://www.equator-network.org/reporting-guidelines/spirit-2013-statement-defining-standard-protocol-items-for-clinical-trials/).

## Introduction

### Background and rationale {6a}

The reported prevalence of daytime lower urinary tract dysfunctions (LUTD) in children ranges widely from 1 to 20% [1]. Among these, overactive bladder syndrome (OAB) as a storage dysfunction and dysfunctional voiding as an emptying dysfunction are the two main entities. Failure to achieve continence (normally reached by the age of three to four), urgency, frequency, hesitancy, and frequent urinary tract infections (UTIs) are reported complaints. Nocturnal enuresis, without daytime LUTD, is considered as a separate entity and has an estimated prevalence of 5–10% at the age of seven [1].

In the management of both OAB and nocturnal enuresis, the objective is to increase the bladder capacity if reduced for the age. Conservative therapy like lifestyle advice and behavioral modifications, including bladder re-education and bowel management, is the first step in a multimodal approach (urotherapy). In case conservative therapy fails, anticholinergic drugs are the mainstay of medical treatment. As an alternative, in case one is reluctant towards pharmacotherapy or in case pharmacotherapy has failed, peripheral neuromodulation can be offered.

Different types of peripheral neuromodulation have been practiced in the pediatric population like transcutaneous electrical nerve stimulation (TENS)—on the sacrum or over the posterior tibial nerve (TTNS) and percutaneous tibial nerve stimulation (PTNS) [2, 3]. However, to our knowledge, no exact data on how frequently adopted this treatments are, are published.

In our department, PTNS is the alternative treatment for OAB in case there are contra-indications for the use of drug therapy or in case a non-drug therapy is preferred. It is proven to be effective and safe in children with iOAB [4]. However, the time-consuming weekly in-office visits and the percutaneous approach make therapy child-unfriendly. The transcutaneous technique, by contrast, is non-invasive and can be easily applied at home. It would benefit the patient and the parents if TTNS would form an equal alternative to PTNS therapy. Besides few reactions such as skin reactions from the adhesive electrodes, no serious adverse events have been reported in TENS therapy [3, 5].

Ramírez-García et al. conducted a prospective efficacy study on TTNS compared to PTNS therapy as treatments for adults with OAB. The authors could demonstrate the non-inferiority of TTNS in comparison to PTNS in decreasing daytime voiding frequency [6]. However, the non-inferiority of the transcutaneous technique over the percutaneous technique in a pediatric population has not been proven so far.

In the TaPaS trial—acronym for Transcutaneous tibial nerve stimulation, Percutaneous and Sham therapy—we will evaluate both the superiority of TTNS over sham therapy (part I) and the non-inferiority of TTNS compared to PTNS in children with idiopathic OAB (iOAB) (part II).

To our knowledge, only two sham-controlled RCTs have been published on the efficacy of TTNS in children with OAB. In the first study published by Boudaoud et al., 20 children with OAB were randomized into a TTNS and a sham group. The clinical results remained the same between both groups, underlining the potential placebo effect of any type of management in this population [7]. In the second study by Patidar et al. a significant benefit of TTNS over sham therapy in a study population of 40 children with OAB was seen [8]. Since the results of both trials are contradictive, we decided to set up a new similar RCT in order to be able to conduct part II.

### Objectives {7}

The objective of part I of the TaPaS trial is to evaluate the superiority of TTNS therapy over sham therapy. It is set-up as a small clinical trial in order to obtain own data, enabling us to conduct part II. The end objective of the TaPaS trial is to show the non-inferiority of TTNS over PTNS therapy.

### Trial design {8}

A prospective, single-center randomized controlled double-blinded trial is set up, comparing TTNS versus sham therapy. Participants are allocated on a 1:1 ratio to either the intervention arm, either or the control arm, according to a computer-generated list of random numbers. Superiority of TTNS over sham will be assessed.

## Methods: participants, interventions, and outcomes

### Study setting {9}

The recruitment of participants is carried out by pediatric urologists and pediatric nephrologists from the Department of Urology and at the Department of Pediatrics at the academic hospital of the Ghent University (East-Flanders, Belgium). Children attending a pediatric specialist (PS) for urgency incontinence or bedwetting are eligible for inclusion. The inclusion criteria are listed below.

At the initial visit, the child with lower urinary tract symptoms (LUTS) is subjected to a complete diagnostic work-up according to the standard of care [9]. Besides a baseline history-taking assessment, a few additional evaluations are performed: urine sample analysis, a bladder and kidneys ultrasound (US), and an uroflowmetry with an US guided post-void residual (PVR) measurement. A 3 days daytime bladder diary and a 7 nights night-time bladder diary are distributed [10]. Based on the completed bladder diaries and the baseline work-up, children are diagnosed at the second visit and subsequently screened for eligibility.

### Eligibility criteria {10}

Patients who meet the following criteria are eligible for inclusion:
Diurnal urgency urinary incontinence and/or nocturnal enuresis (primary or secondary).Aged from 5 to 12 years old.Being treatment–naïve or only having been treated with urotherapy (see the “Intervention description {11a}” section for a detailed definition of urotherapy).Having a parent or guardian who is able to complete bladder diaries reliably.

Exclusion criteria are the following:
Patients already treated with non-conservative therapies, i.e., any drugs with anticholinergic effect, transcutaneous electrical nerve stimulation (TENS), PTNS, or intradetrusor botulinum toxin injections.Patients with a neurogenic bladder dysfunction.Patients with dysfunctional voiding, diagnosed by the presence of a staccato-shaped curve on uroflowmetry at the moment of screening.Patients with nocturnal polyuria, registered on a 7 days night-time bladder diary. Nocturnal polyuria is defined by the International Children’s Continence Society (ICSS) as a nocturnal urine production exceeding 130% of the expected bladder capacity for age [10].Patients with behavior disorders like attention-deficit hyperactivity disorder.Patients with learning disabilities and/or lack of capacity, unable to comprehend urotherapy”

### Who will take informed consent? {26a}

If a child is eligible for inclusion, the child and parent(s) or guardian are verbally informed about the study by their PS and a written patient information sheet is distributed. If both parties are willing to participate, an informed consent for the parent and an informed consent adapted to minors (from 8 to 12 years old) are signed by the respective parties. Subsequently, an appointment for a first visit at the pediatric physiotherapist is made. A research assistant, also being a medical doctor, can function as an authorized surrogate to take informed consent.

Both the participant and investigator receive a signed copy of the consent form. Paper IC forms are stored and kept confidential in the archives of the data management unit. At all times, the IC form can be requested by the institutional data protection officer.

### Additional consent provisions for collection and use of participant data and biological specimens {26b}

There are no additional informed consents needed since no biological specimens are taken.

## Interventions

### Explanation for the choice of comparators {6b}

The results of the two only RCTs that have been conducted to compare TTNS and sham therapy in children are conflicting [7, 8]. Therefore, we chose to set up a new sham-controlled RCT.

### Intervention description {11a}

#### Intervention group

Active neuromodulation treatment is delivered by the Transcutaneous Electrical Nerve Stimulation (TENS) device from BioMedical Life Systems, the Impulse 3000 T®. The physiotherapist places a round self-adhesive surface electrode (Ø3.2 cm) on the tibia, 2 cm superior from the medial malleolus (the negative electrode). The positive electrode is placed in the middle of the medial foot arch on the conduct of the posterior tibial nerve (see Fig. 1). Stimulation parameters are set on a fixed pulse width of 200 μS and a pulse frequency of 20 Hz. In literature, no consensus is reached on the ideal stimulation settings of TTNS [11]. Most studies report a pulse width of 200 μs [3]. We decided to choose the same frequency (20 Hz) as the previous study by Patidar et al. since significant results in this active treatment arm were seen [8].

**Fig. 1 Fig1:**
[figure not shown]
Application of the TENS device

During the therapy session, parents are instructed by the physiotherapist how to apply the surface electrodes themselves. By increasing the pulse intensity by turning the wheel, the TENS device will be switched on. The pulse intensity (in volt) is increased till a comfortable, painless sensation is felt. While increasing the pulse intensity, no motor responses may occur. During the following 30 min, in-office stimulation is given.

At the end of the session, the same device is given to the parents in order to apply ambulant therapy (AT). Parents are instructed to apply the TENS-device on the ankle of their child 1 h daily during the next 12 weeks (two times 6 weeks with 1 visit at the physiotherapist in between), without changing the fixed settings. The TENS device must always be placed on the same ankle. If habituation to the electrical impulse occurs, the pulse intensity should be set around the perception threshold. The intensity may be increased from 1 to 20 V, but stimulation may never be considered as painful. To conceal the allocation of treatment (effective treatment versus sham) for parents and child, they are told they cannot determine by sensation to which study group they belong. Parents who had previous experience with TENS devices are told they cannot compare this TENS therapy with their own since stimulation settings are each time different for every indication.

#### Sham group

The same TENS device, electrode positioning, pulse frequency (20 Hz) and pulse width (200 μs) as in the intervention group are applied for the sham group. Unlike the intervention arm, the pulse intensity button is set on position number “1,” which is the test button on which no electric current is delivered. Parent and child are told that subsensory stimulation will be delivered, not affecting the outcome as proven earlier in other types of neuromodulation trials [12]. In this way, we counter their worry that no sensation is felt. To discourage children or parents from exceeding number 1, they are told higher stimulations can affect the result of treatment in a negative way.

The same stimulation protocol as for the intervention group (1 h daily during 2 periods of 6 weeks) needs to be followed at home after the first visit. When switching the TENS-device on, they may not exceed number 1. This way, no current is supplied.

To check whether this method of blinding was successful, at the end of the trial, both parent and child are asked to indicate to which group they think they belonged.

#### Urotherapy

Besides neuromodulation, every participant in the trial will receive the same standard Urotherapy. Urotherapy can be defined as a bladder re-education or rehabilitation program aiming for the correction of filling and voiding difficulties [13]. It encompasses the following components [10]:
Education on normal lower urinary tract (LUT) functioning and on how the LUT function of the child differs from normal.Lifestyle advices: counseling on drinking (1,5 L–2 L fluid intake daily) and voiding habits, diet, reduction of caffeine intake, proper stool management, etc.Behavioral modifications: sustaining regular voiding habits and adequate toilet positioning, avoiding holding maneuvers, etc.Regular follow-up and encouragement strategies: specifically for this trial, a follow-up visit at the physiotherapist will occur after 6 (the second visit) and 12 weeks (the third visit) of AT.Registration of symptoms, drinking, voiding, and stool habits through diaries.

Specifically for this trial, a 1-day bladder diary must be completed consistently every week as part of the urotherapy. Additionally, 3 times weekly, the participant must try to hold up urine for 5 min if the urge to urinate comes up. Gradually, the duration of delayed urinating should be trained to be increased. The so-called supervoids are part of urotherapy.

In the sixth week, a 7 day night-time bladder diary must be completed. After the second visit at the physiotherapist, the participant must continue the stimulation and urotherapy (plus completion of the diaries and supervoids) for another 6 weeks.

After the third visit, an observation period of 6 weeks is carried out during which no stimulation is given. Urotherapy however should be continued.

### Study schedule

For a structured overview of the study schedule, see Fig. 2 and Table 1. After enrolment, the participant is referred to the physiotherapist for a first visit (t_1_). Urotherapy and a first neuromodulation session are given. After home-therapy for 6 weeks, a second evaluation visit at the physiotherapist is planned (t_2_). Together with the parent and participant, the progression in symptoms is evaluated by review of the completed diaries. After the second 6-week period of home-therapy, a third follow-up visit at the physiotherapist is planned (t_3_). Primary outcomes are collected and delivered to the research assistant. At this point (at 12 weeks), the degree of clinical response to the treatment will be assessed. “No response” is defined as less than 50% increase in the average voided volume (AVV) compared to baseline, registered in the bladder diary. “Partial response” is predefined as 50–99% increase in the AVV, and “Complete response” as a 100% increase in AVV [10].

**Fig. 2 Fig2:**
[figure not shown]
CONSORT flowchart of the TaPaS trial part I

**Table 1 Tab1:**
[figure not shown]
Schedule of enrolment, interventions and assessments

To evaluate the duration of clinical response, a third period of 6 weeks without any treatment (the observation period) is inserted. During this “wash-out” period, the same set of bladder diaries must be completed.

The study is closed at the end of the last follow-up visit at 18 weeks at the treating PS (t_4_). The PS will be briefed beforehand to which treatment arm the participant was allocated. The same assessment as during baseline will be repeated and the parent and participant will be unblinded during this follow-up visit.

For post-trial care, see item 30.

### Criteria for discontinuing or modifying allocated interventions {11b}

In case a dermal allergic reaction from the self-adhesive electrodes as an expected adverse event would occur, hypoallergenic electrodes will be provided to the participants, free of charge. On the participant’ request, the therapy can be discontinued at any time in the course of the study. No reason for this request should be given. In case symptoms would improve or worsen during therapy, no modifications to the stimulation protocol are allowed.

### Strategies to improve adherence to interventions {11c}

At the first study visit, extensive counseling of the importance of therapy compliance is given to the parents. Adherence to therapy will be stimulated by the required completion of bladder diaries and the active encouragement of the participant and parent by the physiotherapist during the 6-weekly follow-up visits. During the follow-up visits, the potential progression of symptoms will be actively evaluated by going through the completed diaries, together with the participant.

To check the adherence to the treatment protocol by the participant, registration of the performance and duration of daily TENS-application in a diary will be requested.

### Relevant concomitant care permitted or prohibited during the trial {11d}

During the trial, the following bladder medication may not be taken: Anticholinergic drugs and a β3 receptor agonist (i.e., mirabegron). Medication to stimulate bowel movement and treat constipation (such as laxative) are permitted. Another form of neuromodulation like sacral TENS is prohibited.

### Provisions for post-trial care {30}

The study is closed at 18 weeks. Participants who had received partial or complete clinical success at 12 weeks (independently from the allocated group) can either choose to stop any further treatment or receive further therapy along the standard of care (i.e., bed-wetting alarm if enuresis is still present, pharmacotherapy or percutaneous tibial nerve stimulation (PTNS)).

If participants belonged to the sham group and did not perceived clinical success, voluntary enrolment in part II of the TaPaS trial is possible, wherein TTNS will be compared to PTNS therapy. No financial support for post-trial care will be provided.

### Outcomes {12}

All outcomes will be assessed after 12 weeks of treatment and will be compared to baseline measures.

Outcomes will be reported both as:
Median (IQR) absolute change from baseline − median (IQR) percentage change from baseline.

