##### Parents reported satisfaction of urinary symptoms

Parents are asked to rate the following question: ‘How would you feel as a parent or guardian if your child’s bladder symptoms were to remain as they are on at this moment?” A score on a Likert-scale from 1 (extremely dissatisfied) to 7 (extremely satisfied) at baseline and after 12 weeks of treatment must be given.

The parent or guardian is the most trustworthy source to obtain a subjective assessment. Therefore, a parent reported instead of patient reported outcome is obtained.

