### Statistical methods

#### Statistical methods for primary and secondary outcomes {20a}

Statistical analyses will be performed using SPSS version 25.0. Descriptive statistics of demographic characteristics will be presented by median and interquartile ranges (IQR) for continuous variables and frequencies and percentages for categorical variables. Since the small sample size, non-parametric tests will be chosen. In case a subject withdraws early, a new participant will replace them till the required sample size is reached. An ITT will be performed. If case data are missing, missing data will be imputed via multiple imputation.
° Intra-arm analyses (baseline vs. 12 weeks):Baseline and 12 weeks follow-up absolute values and absolute change and percentage change from baseline values will be presented as medians (IQR). Intra-arm analyses will be assessed using a two-sided Wilcoxon signed rank test.° Inter-arm analyses (sham versus TTNS therapy): differences in absolute and percentage change from baseline between both groups will be reported as medians (IQR) and will be presented with a 95% confidence interval.

Inter-arm analyses will be assessed using a two-sided the Mann-Whitney *U* test

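### Percentage change, with its between-arm test, is prescribed without exception and so covers the 1–7 parent satisfaction score, where it depends on how the scale is numbered

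*Protocol article*

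**What the plan says.** Outcomes {12} opens with a general statement, "All outcomes will be assessed after 12 weeks of treatment and will be compared to baseline measures", and then says outcomes are reported in two forms: "Median (IQR) absolute change from baseline" and "median (IQR) percentage change from baseline". No outcome is exempted.

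Statistical methods for primary and secondary outcomes {20a} carries both forms into the between-arm comparison: "differences in absolute and percentage change from baseline between both groups will be reported as medians (IQR"), with a 95% confidence interval. The test follows: "Inter-arm analyses will be assessed using a two-sided the Mann-Whitney" U test. No baseline adjustment is stated.

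The section on parents' reported satisfaction defines the outcome as one question: "A score on a Likert-scale from 1 (extremely dissatisfied) to 7 (extremely satisfied) at baseline and after 12 weeks" of treatment. It neither mentions percentage change nor exempts the score from it. Plans for assessment {18a} describes the scale as non-validated.

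The Methods paragraph of the abstract words the outcomes differently from one another. It speaks of a percentage difference for supervoid volumes, incontinence episodes and voiding frequency, but for this outcome only of "the difference in parent reported outcomes between baseline and after 12 weeks of treatment".

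**The concern.** A percentage change needs a scale with a true zero. Millilitres and void counts have one. A seven-category satisfaction item does not: its lowest category is called 1 by convention. Dividing by the baseline label therefore gives a number that reflects the labelling and the starting category as much as the improvement.

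A rank test does not remove the problem. Mann-Whitney ignores the spacing of values but uses their order, and dividing by baseline changes the order.

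The plan as written produces two between-arm tests for this outcome, one on a usable scale and one not. If they disagree, the article does not say which is the result. This is the only parent-reported outcome, and the article itself regards the parent as the best source of a subjective assessment.

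**Working it through.** **No figure of the plan's own to reproduce.** The article gives no assumed mean, SD or effect for satisfaction. The 12 per arm comes from Sample size {14}. All distributional inputs below are assumptions.

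**1. Scale arithmetic (no assumptions).** Percentage change = 100 × (12-week score − baseline) / baseline, so one step up = 100 / baseline.

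- From 1: 100/1 = +100%. From 4: 100/4 = +25%. From 6: 100/6 = +17%.

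The same two-step gain under two codings of the same answers:

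| Baseline (1–7 coding) | % change, 1–7 coding | % change, 0–6 coding | Absolute change, either coding |
|---|---|---|---|
| 1 | 200 | undefined (2/0) | +2 |
| 2 | 100 | 200 | +2 |
| 3 | 67 | 100 | +2 |
| 4 | 50 | 67 | +2 |
| 5 | 40 | 50 | +2 |

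**2. Order of patients.** A move from 1 to 3 is 100 × 2/1 = +200%. A move from 4 to 7 is 100 × 3/4 = +75%. The second gained more steps but ranks lower. The order also depends on the coding. Moves from 2 to 3 and from 4 to 6 tie at +50% under 1–7 coding (100 × 1/2 and 100 × 2/4). Under 0–6 coding they become +100% (100 × 1/1) and +67% (100 × 2/3).

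**3. Power and agreement of the two tests.** Simulation with 12 per arm: baseline mostly 1–3 with the same distribution in both arms, change SD 1.3 steps, true mean gains of 2.5 versus 1 step, and a two-sided Mann-Whitney test at 5% on each scale. Several runs with somewhat different assumed baselines gave:

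- absolute change: power 68–71%;
- percentage change: power 48–55%;
- the two verdicts differ in 22–26% of trials.

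**4. Type I error.** With no effect and equal baseline distributions (probabilities 0.30, 0.35, 0.25, 0.10 on scores 1–4; gains of 0–3 steps with probabilities 0.2, 0.3, 0.3, 0.2; 5,000 trials), rejection was 3.9% on absolute and 4.4% on percentage change. Neither is inflated.

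**5. What baseline imbalance does, and how often it occurs.** With no effect, but arms drawn from populations with mean baselines of 1.7 and 2.6 (a gap of 0.9), rejection was 17% on percentage change and 4.7% on absolute change. The percentage medians differed by about 35 points on average.

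Gaps of that size are uncommon under 1:1 randomisation. The SD of a difference in means is SD × √(2/12). For assumed baseline SDs of 0.96 and 1.21 this is 0.39 and 0.49, so 0.9 points lies 2.3 and 1.8 SDs out. Simulated frequencies:

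| Baseline gap, either direction | SD 0.96 | SD 1.21 |
|---|---|---|
| 0.9 or more | about 2.5% | about 8% |
| 1.5 or more | 0.01% | 0.3% |

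Among no-effect trials with an ordinary gap of 0.3–0.5, the percentage test rejected in about 4%.

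**The case against.** The strongest reply is that the plan already contains the right analysis. Absolute change is prescribed beside percentage change, and {20a} also presents the baseline and 12-week values. The absolute test keeps its full power, so the loss falls only on a second, redundant summary. That stands, and it is the main reason the point is minor. It does not settle which test governs when the two disagree.

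A second reply is that the general rule was never meant literally. Duration of effect, in weeks, has no baseline and cannot be a change of either kind, and the abstract's wording suggests that a plain difference was intended for satisfaction. That is a fair reading of intent, and it supports the fix. But the methods text is what an analyst will follow, and it makes no exception. Nor should the abstract and methods be called a flat contradiction: a plain difference is compatible with absolute change reported alongside another summary. The wording is unaligned, no more.

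A reader might also infer that the percentage test will create false treatment effects from chance baseline imbalance, especially as Sequence generation {16a} states no stratification. The documents do not support that as the main concern. Randomisation keeps the overall error rate near 4–5%, and the distortion needs baseline gaps that are uncommon. Absolute change is not wholly immune to imbalance either, because of floor and ceiling effects and regression to the mean.

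**Conclusion.** The point holds and is minor. As written, the rule yields a percentage-change summary and test for a 1–7 ordinal item whose value and patient ordering depend on the numbering of the categories. That part is arithmetic and needs no assumption.

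The practical size is about 70% power on absolute against about 50% on percentage change, with differing verdicts in about a quarter of trials. These figures rest on assumed baselines, spread and effect, because the article gives no satisfaction data. They would move with other inputs; the scale dependence would not.

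The finding does not extend to an inflated overall type I error. Nor does it reach the primary outcome: AVV is a volume with a true zero, so the arbitrary-origin objection does not apply there.

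**What to change.** In Outcomes {12} and Statistical methods {20a}, add one sentence limiting percentage change to the ratio-scale measures. State that parent satisfaction is summarised and compared by absolute change only, or by the 12-week score adjusted for baseline, with one of the two named in advance. This brings the methods into line with the abstract.

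The cost is one sentence. It removes one summary and one test, needs no new data and leaves the primary analysis as it is.

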##### Number of urgency incontinence episodes during daytime and night-time

This is the median change of urinary incontinence episodes compared to baseline registered in a 3 days daytime bladder diary and night-time bladder diary (the average of 7 nights).

For parents and participants, this is the most relevant clinical outcome since it significantly affects daily activities mostly.

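### Percentage change in incontinence episodes is tested between arms, but it has no value for children with no daytime or no night-time episodes at baseline

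*Protocol article*

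**What the plan says.** All references are to the protocol article.

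- **Scale.** Outcomes {12} gives one format for all outcomes: absolute change, as a median with IQR, and "median (IQR) percentage change from baseline". The abstract (Methods) lists as secondary endpoints "the percentage difference in supervoid volumes, number of urinary incontinence episodes/24 h and in voiding frequency". It gives no absolute version for these.
- **Test.** Statistical methods for primary and secondary outcomes {20a} reports between-arm differences in both absolute and percentage change, with a 95% confidence interval and a two-sided Mann-Whitney U test.
- **Outcome definition.** The outcome headed "Number of urgency incontinence episodes during daytime and night-time" is a median change from baseline, "registered in a 3 days daytime bladder diary and night-time bladder diary (the average of 7 nights". Its definition does not mention percentages and does not say how the two diaries are combined. The same section calls this the most relevant clinical outcome for families.
- **Who enters.** Eligibility criteria {10} requires "Diurnal urgency urinary incontinence and/or nocturnal enuresis (primary or secondary", with no minimum number of episodes. The baseline form in {18a} likewise records daytime incontinence and enuresis as symptoms that need not occur together.

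**The concern.** A percentage change divides by the baseline value. The entry criteria admit children whose baseline is zero for one of the two components: an enuresis-only child has no daytime episodes, and a daytime-only child has no wet nights. For them the prescribed quantity does not exist, and a rank test cannot place them. The article gives no rule for a zero baseline.

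At stake is the percentage comparison of a secondary outcome that the article itself ranks highest for families. If the affected children are left out, that comparison covers a subset selected by symptom type and not the intention-to-treat population named in {20a}. Randomisation is unstratified ({16a}), so the omissions need not balance between arms.

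**Working it through.** The plan states no figure for this point, so there is none to reproduce. The planned size of 24, 12 per arm (Sample size {14}), is used only as a denominator.

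**1. When the quantity exists.** Let B be the baseline count and F the 12-week count over the same diary length. Percentage change = 100 × (F − B)/B.

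- B = 0, F = 0 gives 0/0, which has no value.
- B = 0, F = 2 gives 2/0, which has no value.
- Absolute change F − B is 0 and 2 in these cases, so it is always defined.

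**2. Stability at low counts.** One more episode in the three-day diary is always +1/3 episode per day in absolute terms. From B = 1 to F = 2 it is +100%; from B = 10 to F = 11 it is +10%.

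**3. How many children.** The documents do not give the share m with a zero baseline in a component, so m is assumed. The expected number without a value is 24 × m. The chance of at least one, treating children as independent, is 1 − (1 − m)^24.

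| Assumed m | Expected without a value | Average left per arm, 12 × (1 − m) | Chance of at least one |
|---|---|---|---|
| 10% | 2.4 | 10.8 | 92% |
| 20% | 4.8 | 9.6 | 99.5% |
| 30% | 7.2 | 8.4 | >99.9% |
| 50% | 12 | 6 | >99.9% |

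These rows apply to day and night taken separately.

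**4. Zeros by chance in a child who has the symptom.** With an assumed Poisson rate r per day, the chance of no episode in three days is exp(−3r). This is 22% at r = 0.5 and 5% at r = 1. With an assumed average of one wet night per week, the chance of none in seven nights is (1 − 1/7)^7 = 34%. These figures ignore screening. Study setting {9} bases diagnosis and eligibility on the completed diaries together with the work-up, which should make such zeros less common.

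**5. If day and night are summed.** The abstract's count per 24 h could be the daytime episodes per day plus the wet nights per night. An enuresis-only child with, say, four wet nights in seven would then have a baseline of 0 + 4/7 = 0.57, and the percentage change exists. Every eligible child has at least one symptom, so most zeros from step 3 would disappear and only chance zeros would remain. The outcome section does not say that the counts are summed.

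**The case against.** The strongest reply is that the plan already contains the remedy. Absolute change is prescribed beside percentage change and is compared between arms, and the section defining the outcome does not ask for a percentage. This stands. A reader might infer that the incontinence outcome itself is undefined, or that its between-arm comparison abandons the randomised set; neither holds for absolute change.

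Second, the endpoint in the abstract is per 24 h, which on a plain reading combines day and night. That may remove most zeros. It does not settle the matter, because the full definition keeps two diaries of different length and gives no combining rule.

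Third, a zero-baseline rule could be in an analysis plan that is not shown. That would be an answer if the article were merely silent. Here it fixes a measure and a test that have no value for some eligible children.

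Two further readings go too far. One is that the undefined values would be imputed as missing: {20a} and {20c} apply imputation to missing data, a recorded zero is not missing, and nothing says that it would be treated so. The other is that the plan analyses the 1–7 satisfaction score as a percentage. Only the general wording in Outcomes {12} and {20a} reaches that far, and the abstract speaks simply of a difference for parent-reported outcomes.

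**Conclusion.** The point holds for the percentage version only. As written, percentage change in incontinence episodes is undefined for children without daytime, or without night-time, episodes at baseline, and it is erratic at low counts. The logic needs no assumption beyond the entry criteria and the separate diaries.

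The size is not known. On assumed zero-baseline shares of 10% to 50% per component, about 2 to 12 of 24 children would have no value. If day and night are summed, the number would probably be small. The range shows what could happen and is not an estimate.

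The effect is confined to one secondary outcome. Average voided volume is unaffected, as are the sample size and the decision to start part II. The plan should be corrected because a stated test cannot be carried out as described on all randomised children, and because the handling of zeros should not be chosen after the results are known.

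**What to change.** - In Outcomes {12} and {20a}, make absolute change the only inferential scale for incontinence episodes, in all randomised children. Report daytime episodes per day and wet nights per week separately.
- Preferably take the baseline count into account, for example with a rank-based analysis of covariance, which keeps to the plan's non-parametric approach. Children without the symptom at baseline will mostly show no change and so dilute the comparison; this is the price of keeping everyone in.
- Align the abstract's per-24-hour percentage endpoint with the outcome section. If a combined count is wanted, state how the 3-day and 7-night diaries are put on one scale.
- If percentage change is kept, report it descriptively only, in children with a non-zero baseline for that component, and state the denominator. Testing it in those children would amount to a subgroup analysis, which {20b} rules out.
- As a minor clarification, state that the general percentage format does not apply to the satisfaction score.

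The cost is wording only: no new data, visits or participants. The change should be made before the research assistant is unblinded, which {17b} places after data entry.
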